Patients with MCI, ASD, and ADHD frequently exhibit epileptiform discharges on electroencephalography (EEG) recordings, resting-state hyperactivity on functional magnetic resonance imaging (fMRI), and lower cortical excitability thresholds measured with transcranial magnetic stimulation (Takarae and Sweeney, 2017; Targa Dias Anastacio et al., 2022; Ugarte et al., 2023). In AD, subclinical epileptiform activity (SEA)—epileptiform discharges without overt clinical seizures—is increasingly recognized as a major contributor to accelerated cognitive decline (Kamondi et al., 2024; Vossel et al., 2026). Long-term EEG studies have demonstrated that SEA in AD is associated with faster cognitive deterioration and specific neuroanatomical substrates, including early precuneus thinning and larger general cortical volumes (Horvath et al., 2019; Nous et al., 2024). Previous observations have shown that sleep EEG is particularly sensitive to detect epileptiform activity in dementia (Horváth et al., 2017; Nous et al., 2024; Vossel et al., 2016). Some studies also suggest that SEA in dementia is associated with a special, probably more aggressive neuroimaging phenotype of AD (Cretin et al., 2016). Earlier reports have also demonstrated that SEA is linked to more rapid progression of cognitive decline in AD (Horvath et al., 2021; Vossel et al., 2013, 2016).

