To generate normative EEG values, we perform meticulous EEG preprocessing on 24-h recordings—artifact removal (e.g., eye blinks, muscle noise), filtering, and referencing—to ensure clean data. Two manual expert reviews of the files to identify potential SEA in line with the previously published protocols (Kamondi et al., 2024; Port et al., 2019). To define normal limits, the density, amplitude, duration, and spatial distribution of these events can be quantified across all control recordings. Statistically, normal values are represented by upper tolerance limits (the 95th percentile) of spike density (events per hour) computed from the control group. Normative modeling is applied to further refine these thresholds by accounting for age, sex, sleep state, and recording montage, variables known to influence EEG background and transient patterns. Additionally, spectral power and band ratios (delta, theta, alpha, beta, gamma) are used to construct normative baselines, against which epileptiform spikes produce transient deviations.

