#### In-ward protocol

2.4.2

Participants will be admitted to a dedicated video-EEG monitoring unit for three consecutive days and nights.

Continuous video-EEG: 34-channel scalp EEG (Micromed Morpheus, 10–20 system) will be recorded throughout admission, with peri-orbital leads for sleep staging.Memory paradigms: Three parallel versions of the RAVLT will be administered on consecutive evenings (7 pm).○Immediate recall (five learning trials) and delayed recall at 30 min.○Morning recall at ∼9 am to assess overnight retention.

Sleep analysis:○Visual staging of 20-s epochs according to AASM criteria (Moser et al., 2009).○Artifact annotation in 4-s segments.○Automated slow and fast spindle detection with Individual Adjustment Method (Bódizs et al., 2009).○Quantification of spindle density, duration, amplitude, and frequency over frontal (slow spindles) and centro-parietal (fast spindles) leads, in N2 and N3, and combined N2+N3.○Power spectral analysis of N2 and N3 for slow-wave sleep characteristics.Serial blood sampling: Evening and morning samples across the 3-day stay to estimate circadian patterns of plasma tau and Aβ.

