#### Data extraction and mechanistic analyses

2.4.3

For each participant, we will derive:

SEA density and temporal distribution across nights and days.Within-subject variability in RAVLT learning, 30-min retention, and overnight consolidation.Sleep architecture metrics and spindle parameters.Day–night and day-to-day changes in plasma tau/Aβ.

SEA density will be correlated with memory performance, spindle metrics, and biomarker levels, as assessed using mixed-effects models that account for repeated measures. Comparisons will be made between SEA-rich and SEA-poor epochs and between days with high vs low hyperexcitability burden. Group-specific patterns (e.g., MCI vs ASD vs ADHD) will be examined.

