#### Mechanistic analyses

2.6.2

Linear mixed-effects models will relate within-subject variation in SEA density to RAVLT performance, sleep spindle parameters, and plasma tau/Aβ levels, with random intercepts for participants.Connectivity changes (morning vs evening, SEA-rich vs SEA-poor epochs) will be assessed with paired tests and network-based statistics.Mediation models will explore whether sleep spindle disruption mediates the effect of SEA on overnight memory consolidation.

Effect sizes, confidence intervals, and model diagnostics will be reported systematically.

The entire analysis pipeline is highlighted in Figure 2.

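### The SEA-rich versus SEA-poor epoch contrast has no stated control for sleep stage, so a connectivity difference could not be attributed to SEA

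*Protocol article*

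**What the plan says.** Section 2.4.2 (In-ward protocol) has continuous video-EEG over three days and nights, "recorded throughout admission, with peri-orbital leads for sleep staging", with "Visual staging of 20-s epochs according to AASM criteria".

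Section 2.4.3 derives "SEA density and temporal distribution across nights and days" for each participant and adds: "Comparisons will be made between SEA-rich and SEA-poor epochs and between days with high vs low hyperexcitability burden". Section 2.6.2 names the test: "Connectivity changes (morning vs evening, SEA-rich vs SEA-poor epochs) will be assessed with paired tests and network-based statistics". It also says: "Linear mixed-effects models will relate within-subject variation in SEA density to RAVLT performance", as well as to spindle parameters and plasma tau/Aβ, with random intercepts for participants. Neither section names sleep stage as a matching factor, stratum or covariate, and SEA density is divided by night and day only.

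Two other places show that the authors regard state as important. Section 1.1 says that "sleep EEG is particularly sensitive to detect epileptiform activity in dementia". Section 2.4.1 refines the normative EEG thresholds by "accounting for age, sex, sleep state, and recording montage, variables known to influence EEG background and transient patterns".

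**The concern.** On the article's own account, sleep state is linked to the exposure (how readily discharges appear) and to the outcome (background EEG, from which epoch-level connectivity would be computed). That makes it a confounder of the epoch contrast. State is accounted for in the normative thresholds, but no such control is stated for the within-person comparisons, where stage varies most.

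Paired tests and random intercepts remove stable differences between people. They leave stage untouched, because one person passes through wake, N2, N3 and REM within each day. If SEA-rich epochs contain more NREM than SEA-poor epochs, the paired difference carries a sleep-stage difference even when SEA has no effect on connectivity.

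A related, smaller problem touches the overnight memory models. If discharges are more frequent in NREM, a night with more NREM has a higher SEA density at unchanged excitability. If NREM time also affects retention, the two become associated without any effect of SEA.

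**Working it through.** The plan states no figure to reproduce here. The question is how far stage could distort the contrasts if the true SEA effect is zero.

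**Assumed inputs (none is in the documents).** NREM 6.25 h per 24 h; 5-minute epochs, giving 75 NREM and 213 other epochs; 2 discharges per hour outside NREM, i.e. 2/12 = 0.167 per epoch; NREM rate r times higher, with r = 2, 3 or 5; Poisson counts; SEA-rich means at least one discharge. The article defines neither epoch length for this contrast nor the cut for SEA-rich.

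**Step 1. Stage mix of the two sets of epochs.** The chance that an epoch is SEA-rich is 1 − exp(−0.167) = 0.1535 outside NREM and 1 − exp(−0.167r) in NREM. The expected number of SEA-rich epochs outside NREM is 213 × 0.1535 = 32.7, leaving 180.3 SEA-poor.

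| r | P(rich) in NREM | SEA-rich NREM epochs | NREM share of SEA-rich | NREM share of SEA-poor |
|---|---|---|---|---|
| 1 | 0.1535 | 11.5 | 11.5/44.2 = 26.0% | 63.5/243.8 = 26.0% |
| 2 | 0.2835 | 21.3 | 21.3/54.0 = 39.4% | 53.7/234.0 = 23.0% |
| 3 | 0.3935 | 29.5 | 29.5/62.2 = 47.4% | 45.5/225.8 = 20.1% |
| 5 | 0.5654 | 42.4 | 42.4/75.1 = 56.5% | 32.6/212.9 = 15.3% |

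A 2,000-repeat simulation of the same set-up gave 40%, 48% and 57% for SEA-rich epochs at r = 2, 3 and 5.

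**Step 2. Spurious contrast.** If connectivity differs between NREM and other states by d standard deviations, the expected unmatched difference with no SEA effect is d × (share in SEA-rich − share in SEA-poor). At r = 3 the gap is 47.4% − 20.1% = 27.3 points, so d = 0.3 gives 0.08 SD and d = 0.8 gives 0.22 SD. At r = 1, or d = 0, it is zero.

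**Step 3. What a test does with that.** A simulation used 40 participants (the substudy's expected final sample, section 2.2.4), NREM at a quarter of 24 h, a true SEA effect of zero and a nominal two-sided 5% level. There were 300 runs per scenario. The entries are false-positive rates for d = 0.3 and d = 0.8.

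| r | 24 h, unmatched | Night only, unmatched |
|---|---|---|
| 2 | 18% and 66% | 10% and 23% |
| 3 | 34% and 97% | 17% and 64% |
| 5 | 67% and 99.7% | 30% and 91% |

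Comparing SEA-rich with SEA-poor epochs inside NREM gave 3–8% in every scenario, i.e. nominal within simulation error. The unmatched percentages also move with the assumed discharge rate and epoch noise. They show direction and are not a forecast.

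**Step 4. Overnight density.** With 8 h in bed, h hours of NREM and constant excitability, density is proportional to (r·h + 8 − h)/8. For h = 6 against h = 4 the ratio is 14/12 = 1.17 at r = 2, 20/16 = 1.25 at r = 3 and 32/24 = 1.33 at r = 5.

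In a simulation of 40 participants over 3 nights, memory depended only on NREM hours (0.3 to 0.5 SD of memory per SD of NREM hours). Relating memory to whole-night density gave false-positive rates of 12–26%, 24–52% and 39–72% at r = 2, 3 and 5. Using SEA per hour of NREM gave 4–6% in every scenario.

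**The case against.** The strongest reply is that the article condenses its mechanistic plan into a few sentences. It does not say that epochs will be unmatched, pooled over 24 h, or drawn from both sleep and wake, and a fuller document may settle this. That stands as a caution. However, the article names the contrast, the test, the exposure and the random effects, and elsewhere singles out sleep state as influential. Followed as written, the named analysis is confounded. Drawing epochs from the night alone reduces the problem without removing it.

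A reader might infer more than the documents support:

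- **That SEA-rich epochs will be mostly NREM, or that the contrast will largely reflect sleep versus wake.** No stage-specific rates are given, and in the working NREM passes half of SEA-rich epochs only at r = 5. Section 1.1 speaks of sensitivity of sleep EEG, and in dementia. It does not say that most discharges occur in sleep, and the substudy spans HC, MCI, ASD and ADHD.
- **That the association in Hypothesis 8 would be reversed.** No model with NREM time as the outcome is stated. Spindle measures are taken within N2 and N3, so more NREM time does not mechanically raise spindle density, amplitude or duration.

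It is also fair that stage may lie on the causal path. If SEA disrupts sleep, conditioning on stage can remove part of the effect of interest, and total overnight burden is a defensible exposure. This argues against replacing overall density with a stage-specific rate. It does not argue against matching in the epoch contrast.

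Finally, section 2.2.4 labels mediation and diagnostic subgroup comparisons exploratory, and section 3.5 disclaims definitive causal inference. The exploratory label is not extended to the epoch contrast or the mixed models, and section 3.1 claims stronger inference about temporal relationships from the within-subject design.

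**Conclusion.** The point holds for the epoch contrast: as described, a connectivity difference between SEA-rich and SEA-poor epochs cannot be attributed to SEA. The bias arises if SEA rate and connectivity both differ by stage. It runs from none to dominant across the assumed range, and the documents do not locate the study within it.

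A smaller version applies to overnight memory models using SEA density not separated by stage: 17% to 33% higher density for 6 h rather than 4 h of NREM, under the assumed rate ratios of 2 to 5. It is weaker for spindle measures within N2/N3. The issue is confined to the mechanistic substudy and leaves the primary outcome untouched. It should be corrected because the remedy uses data already planned.

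**What to change.** In sections 2.4.3 and 2.6.2:

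1. Select SEA-poor comparison epochs within participant from the same sleep stage (or wake) and a similar time of night or day as each SEA-rich epoch, and run the paired tests and network-based statistics on these matched sets.
2. In the overnight memory, spindle and sleep-architecture models, report SEA rate per hour of N2+N3 alongside overall SEA density. State that conditioning on stage may remove part of any effect acting through sleep architecture, so the two results answer different questions.

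The cost is wording and some programming. Sleep staging and the temporal distribution of SEA are already to be derived, so no new data are needed. The drawback is fewer usable epochs in participants whose SEA falls almost wholly in one stage; the number lost should be reported.

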**FIGURE 2 F2:**
[figure not shown]
Multimodal biomarker domains integrated in the LENDÜLET protocol. ACE, Addenbrooke Cognitive Examination; MMSE, Mini-Mental State Examination; TMT, Trail-Making Test; RAVLT, Rey Auditory Verbal Learning; BDI, Beck Depression Inventory; STAI, Spielberger State and Trait Anxiety Questionnaire; BFC, Benson Figure Copy; Aβ, amyloid-beta; REM, rapid eye movement sleep; MRI, magnetic resonance imaging; sMRI, structural magnetic resonance imaging; fMRI, functional magnetic resonance imaging; DTI, diffusion tensor imaging, FA, fractional anisotrophy; MD, mean diffusivity; LC, local correlation; ICC, intrinsic connectivity; fALFF, fractional amplitude of low frequency fluctuations; SEA, subclinical epileptiform activity.

## Expected results and implications

3

This protocol outlines a comprehensive, multimodal approach to characterizing the association between cortical hyperexcitability and cognitive decline across neurocognitive disorders with high vulnerability to epileptic activity, namely MCI on the AD continuum, ASD, and ADHD. By integrating ambulatory and in-ward EEG, resting-state fMRI, structural MRI, detailed neuropsychology, sleep metrics, and tau/amyloid biomarkers, the LENDÜLET Neurocognitive Research Project seeks to move beyond descriptive associations and toward a mechanistic understanding of how SEA and network hyperactivity affect cognition and disease trajectories.

### Positioning within existing literature

3.1

Previous work in AD and MCI has demonstrated that SEA is more prevalent than previously recognized and is associated with faster cognitive decline (Horvath et al., 2020; Kamondi et al., 2024; Vossel et al., 2026). Similarly, in ASD and ADHD, converging data from EEG, fMRI, and TMS studies point to altered excitation–inhibition balance, resting-state hyperconnectivity or hypoconnectivity in large-scale networks, and increased seizure risk (Beare et al., 2017; Hull et al., 2017; Konrad and Eickhoff, 2010; Liu et al., 2022; Salpekar, 2018; Vilela et al., 2022). However, existing studies have typically focused on single modalities, heterogeneous samples, or narrow diagnostic categories, and have rarely incorporated sleep-dependent memory consolidation or AD-related proteinopathies.

The present study will address these gaps in several ways:

It applies a unified multimodal protocol across four groups (MCI, ASD, ADHD, HC), enabling direct comparison of hyperexcitability prevalence and signatures across disorders and relative to healthy aging.It combines EEG-defined SEA and fMRI-defined network hyperactivity, providing a cross-modal view of hyperexcitability at both fast electrophysiological and slower hemodynamic timescales.It embeds hyperexcitability within a broader framework of structural volumetry, white matter integrity, network connectivity, sleep architecture, sleep spindles, and tau/amyloid burden, thereby situating SEA and hyperactivity in the context of neurodegeneration and systems-level network reorganization.It includes an in-ward mechanistic substudy with repeated within-subject measures, enabling stronger inference about temporal relationships between hyperexcitability, sleep dynamics, and memory consolidation.

By integrating these elements, the LENDÜLET project will be well-positioned to test the overarching hypothesis that cortical hyperexcitability is not merely an epiphenomenon but a mechanistically relevant substrate linking disrupted network dynamics to cognitive decline.

### Conceptual implications: hyperexcitability as a transdiagnostic mechanism

3.2

If our hypotheses are confirmed, the findings will support the notion that cortical hyperexcitability is a transdiagnostic mechanism cutting across traditional categorical diagnoses. Several conceptual implications follow and are summarized in Figure 3:

**FIGURE 3 F3:**
[figure not shown]
A comprehensive overview of the proposed mechanistic connection between neural changes related to hyperexcitability and their applicaability as implication for future biological, clinical and therapeutic experiments. EEG, electroencephalography; fMRI, functional magnetic resonance imaging; TMS, transcranial magnetic stimulation; TDCS, transcranial direct current stimulation.

Shared hyperexcitability phenotype across neurocognitive disorders. Elevated SEA incidence and resting-state fMRI hyperactivity in MCI, ASD, and ADHD, relative to healthy controls, would support the presence of cortical hyperexcitability as a transdiagnostic neurophysiological phenotype. Importantly, such findings would not imply that identical pathophysiological mechanisms underlie hyperexcitability across these disorders. Rather, they would suggest that distinct genetic, developmental, and neurodegenerative processes may converge on a common manifestation of disrupted excitation–inhibition balance and network dysfunction, while differing in their underlying molecular drivers, spatial distribution, temporal evolution, and contribution to cognitive impairment (Sohal and Rubenstein, 2019). Consequently, any commonality identified by this study should be interpreted as convergence at the systems-neuroscience level rather than evidence of a uniform disease mechanism.Network-level vulnerability. Associations between hyperexcitability and altered connectivity within the DMN, SN, and AN may clarify why specific networks are repeatedly implicated in both seizure susceptibility and cognitive dysfunction. For example, hyperactivity in posterior DMN hubs (precuneus, posterior cingulate) might simultaneously promote epileptiform discharges and disrupt memory-related network communication (Stam, 2014).Link between hyperexcitability and neurodegeneration. Demonstrating that hyperexcitability co-localizes with specific patterns of cortical thinning and white matter damage, particularly in medial temporal and parietal regions, would strengthen the hypothesis that recurrent SEA and network overactivity signal structural injury as well. In the MCI/AD continuum, associations with unfavorable tau/Aβ profiles would further support a bidirectional relationship between excitability and proteinopathy (Tanaka et al., 2025; Targa Dias Anastacio et al., 2022).Role of sleep and memory consolidation. Findings that hyperexcitability is associated with disrupted sleep architecture, altered N2/N3 power spectra, and reduced or disorganized sleep spindles, together with impaired overnight verbal memory consolidation, would provide a mechanistic bridge between epileptiform activity and long-term cognitive decline. This would be consistent with the view that sleep-dependent memory consolidation is particularly vulnerable to abnormal neuronal synchrony and that nocturnal SEA may exert disproportionate cognitive impact (Li et al., 2022; Slutsky, 2024).Cross-modal concordance. Evidence of concordance between EEG-detected SEA and fMRI hyperactivity at the individual level would validate the use of complementary modalities for detecting hyperexcitability and might enable future stratification strategies that rely on whichever modality is more feasible or sensitive in a given setting (Von Wegner et al., 2018).

It should also be emphasized that the present study is not designed to establish that cortical hyperexcitability plays an identical mechanistic role across MCI, ASD, and ADHD. Instead, the multimodal framework is intended to identify both shared and disorder-specific characteristics of hyperexcitability. Subsequent analyses will therefore examine whether associations between SEA, functional network alterations, structural changes, sleep physiology, and cognitive performance differ between diagnostic groups. These comparisons will help determine whether cortical hyperexcitability represents a common downstream manifestation of distinct disease processes or reflects disorder-specific mechanisms with partially overlapping neurophysiological signatures.

### Implications for future research

3.3

The project is primarily observational, but it is explicitly designed to generate hypotheses and tools for future interventional studies. Key research implications include:

#### Biomarker development and validation

3.3.1

The multimodal dataset will allow derivation of a candidate biomarker panel of cortical hyperexcitability, combining:

SEA incidence, density, and spatial distribution from 24-h and video-EEG recordingsfMRI-based hyperactivity indices and aberrant connectivity patterns within DMN/SN/ANStructural MRI measures (regional cortical volumes/thickness, DTI metrics)Sleep spindle metrics and N2/N3 spectral characteristicsFluid biomarkers (CSF and plasma tau, Aβ40/42, Aβ42/Aβ40 ratio)

The cross-sectional arm will clarify which combinations of these features optimally discriminate hyperexcitability-positive from negative cases, and which best predict cognitive performance. The mechanistic arm will reveal which metrics track short-term fluctuations in excitability and cognition within individuals. Together, these findings can inform the design of composite scores or latent factors that may serve as more robust endpoints for future clinical trials (Toniolo et al., 2020).

